### Details of power calculations and sample size

Body weight was chosen as the primary outcome variable for calculation of sample size. Utter *et al*. [88] reported a 8.1 kg reduction in body weight in obese women following a 12 week lifestyle intervention, incorporating moderate dietary energy restriction in conjunction with exercise. Body weight changed from a baseline ± SD level of 89.9 ± 11.7 to 81.8 ± 10.8 kg following the intervention. This amount of weight loss is associated with improved physical and psychological health in obese women [41,90]. On the basis of these data, and taking into account an expected patient drop-out of up to 10% (based on the drop-out rate in our ongoing trial with breast cancer survivors [91]), recruitment of 50 patients for each group will give us 90% power to detect a difference in body weight of 8 kg at the α level of 0.05.

### Patient inclusion criteria

a. Postmenopausal women (confirmed by plasma estradiol and gonadotrophin measures in all women aged <55) with a BMI > 25 and classified as disease stage I-III. In our experience [91], a high proportion of breast cancer patients (>80%) meet the BMI criteria and would be suitable for participation in the study.

b. Patients must have completed some form of breast cancer treatment at least three months, and not more than 18 months ago.

c. Patients on Tamoxifen and other endocrine treatments but not hormone replacement therapy (HRT) will be included.

d. Patients must be willing and able to attend supervised exercise sessions at least 3 times per week for a period of 24 weeks, with the intention of achieving an 80% minimum compliance target for attendance.

e. Patients must be an exercise pre-contemplator, contemplator or preparer as defined by the Transtheoretical Model [92].

### Patient exclusion criteria

a. Metastatic breast cancer patients and patients with inoperable or active loco-regional disease.

b. Patients following alternative/complementary diets or taking high dose antioxidant supplements.

c. Patients with a physical/psychiatric impairment that would seriously impair their physical mobility.

d. Patients who are currently suffering from severe nausea, anorexia or other diseases affecting health (e.g. arthritis and multiple sclerosis).

e. HRT is not commonly prescribed in women who are recovering from breast cancer treatment, but use of HRT or oral contraceptives within the past four months is an exclusion criteria.

f. Patients who are currently engaged in exercise (two or more times per week for at least 30 min per session during the previous 3 months).

### Supervised exercise

Patients randomised to the dietary and exercise intervention will attend moderate intensity aerobic exercise sessions on three to five days per week for a period of 24 weeks under the supervision of an exercise scientist. To account for differences in daily patterns of fatigue and to minimise attrition, patients will be offered different times to chose from including week-ends. Patients will be encouraged to attend five supervised sessions each week, and must try to attend at least three of the sessions. Patients not able to attend five supervised sessions will be counselled on how they can fit an extra 1–2 home/community-based exercise sessions into their weekly routine. All sessions of physical activity will be recorded in a physical activity log and portable pedometers (Omron Healthcare, UK) will be used to determine the number of steps/distance walked each day. Supervised exercise will be performed in groups of up to eight participants in an exercise room that contains a variety of aerobic exercise equipment. Each session will comprise a 10 minute warm-up period (involving light aerobic exercise and gentle range of motion exercises), 30 min of aerobic exercise at an intensity of 70%–85% heart rate reserve, and a 10 min cool-down period involving lower intensity aerobic exercise and some light stretching. Patients will wear heart rate monitors throughout the exercise sessions and heart rate and ratings of perceived exertion [93] will be assessed at regular intervals. In accordance with the recommendations of Biddle *et al*. [94], patients will be offered a range of aerobic exercise modalities at these sessions (e.g. stepping, cycling, & walking/jogging) to promote enjoyment and to aid compliance to the programme. Patients will be encouraged to use their preferred exercise mode to strengthen the possibility of them maintaining a physically active lifestyle when the supervised exercise programme has been completed. The exercise therapy sessions will use a variety of cognitive-behavioural techniques for promoting exercise adherence as well as positive attitudes and experiences.

### Dietary energy restriction

Patients randomised to the dietary and exercise intervention will be given individualised healthy eating dietary advice and written information: 'Weight Loss On A Plate' (Scottish Dietetic Association). The focus of the verbal advice will be on reducing the patient's total daily calorie intake to 600 kcal below their calculated energy requirements. Individual energy requirements will be estimated from formulae of basal metabolic rate and physical activity level (Scottish Dietetic Association). The aim of this strategy is to induce a steady weight loss of up to 0.5 Kg each week. In addition, the overall quality of the diet will be examined with a view to (i) reducing the dietary intake of fat to ~25% of the total calories, (ii) eating at least 5 portions of fruit and vegetables a day, (iii) increasing the intake of fibre and reducing refined carbohydrates, and (iv) taking moderate amounts of alcohol. Patients will be required to complete a 3 day diet diary pre intervention and then weekly throughout the study. The diary will include one day from the weekend. The diaries from pre intervention and from weeks 6, 12, 18 and 24 will be analysed, looking specifically at macronutrients, using Dietmaster software (SDA Solutions, London, UK) computer dietary analysis package. Once a week, patients will meet with the research assistant who will discuss their individual diet diaries with them and identify ways which they can further improve their nutritional intake. Patients in the control group will be provided with a general healthy eating booklet 'Getting the Balance Right' (British Nutrition Foundation).

### Outcome measures

The intervention will last for 24 weeks, with all outcome variables being assessed in the week before and the week after the intervention period unless otherwise stated.

### Primary outcome measure

#### Body weight and body composition

Patients will be weighed to the nearest 0.05 kg and percentage body fat estimated using bio-electrical impedance (Bodystat 1500, Bodystat Ltd., UK). Waist and hip girths will be measured to the nearest 0.5 cm using an inelastic circumference tape. Body weight will be measured at weekly intervals in the intervention group, whereas bio-electrical impedance analysis and girth measurements will only be performed in the week before and after the intervention period and at the mid-intervention time point of 12 weeks.

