### Randomisation

The minimisation technique [89] will be used to allocate the patients into one of two groups (i) lifestyle intervention group, incorporating moderate dietary energy restriction of 600 kcal per day in conjunction with aerobic exercise training on 3–5 days per week, or (ii) normal care control group. Minimisation will be used to balance the potentially confounding variables of chemotherapy and treatment with Tamoxifen, aromatase inhibitors or no hormone therapy across the groups. Randomisation will be performed by an independent researcher at the Clinical Trials Research Unit, University of Leeds. The intervention will last for 24 weeks, with outcome measures being assessed in the week before and the week after the intervention period and at the mid-intervention time point of 12 weeks. Patients would be recruited over 16 months, ensuring completion of the trial by 22 months and reporting of the data by 24 months.

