### Data Analysis

A mixed factorial ANOVA will be used to assess (i) changes from baseline on all outcome measures following the intervention within patient groups, and (ii) differences in outcome measures between patients in the lifestyle intervention and control groups post intervention. Pearson product moment correlation coefficients (r) will be calculated to determine bivariate relationships among changes in the variables. Statistical significance will be set at *p *< 0.05. All data will be analysed using the SPSS statistical package (SPSS UK Ltd, Woking, U.K.).

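### The ANOVA fixed for body weight is in its classical form a completer analysis, and, separately, the sections disagree on whether controls are weighed at week 12

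*Protocol article*

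**What the plan says.** **Analysis.** The Data Analysis section states "A mixed factorial ANOVA will be used to assess" within-group changes from baseline and between-group differences after the intervention. It covers all outcome measures and uses SPSS. It does not say how many time levels enter the model or how incomplete patients are treated.

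**Sample size.** The section on power calculations chooses body weight as the outcome and says "recruitment of 50 patients for each group will give us 90% power" "to detect a difference in body weight of 8 kg", "taking into account an expected patient drop-out of up to 10" per cent.

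**Timing.** Three places bear on when weight is measured:
- Randomisation: "outcome measures being assessed in the week before and the week after the intervention period and at the mid-intervention time point of 12 weeks".
- Outcome measures: "all outcome variables being assessed in the week before and the week after the intervention period unless otherwise stated".
- Body weight and body composition: "Body weight will be measured at weekly intervals in the intervention group". No time is given for control weights. Impedance and girths are set at baseline, week 12 and after the intervention, without limit to one arm.

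The sections on psychological stress, depression and quality of life name week 12 explicitly. Those on cardiorespiratory fitness and on the blood, saliva and immune markers do not.

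**The concern.** **Completers.** A classical mixed factorial ANOVA needs a value at each level of the time factor. A woman with no final weight leaves the comparison even though she was randomised. The arms differ in what they ask of patients: the intervention arm is to attend supervised exercise three to five days a week for 24 weeks and review diet diaries weekly, while controls receive a booklet. If women who stop the programme lose less weight than those who stay, a comparison of completers favours the intervention.

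**Timing.** Control weight at week 12 is called for by the Randomisation section but not by the Outcome measures default, and the body-weight section does not settle it. No later analysis plan can repair this, because a weight that was not taken cannot be analysed. A week-12 control weight is also what an all-randomised model would use for a control who leaves in the second half.

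**Working it through.** **1. Reproduce the sample size.** Inputs from the power section: difference 8 kg, baseline SD 11.7 kg, α 0.05, power 90%, drop-out 10%. Sidedness is not stated; two-sided is assumed because it returns the stated N.

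- n per arm = 2 × (1.960 + 1.282)² × 11.7² / 8² ≈ 2 × 10.51 × 136.89 / 64 ≈ 44.95, so 45.
- Allowing for drop-out: 45 / 0.90 = 50 per arm, as stated.
- Power at 45 per arm is 90.0% (normal approximation) or 89.4% (noncentral t).

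The alternatives do not give 50. The post-intervention SD of 10.8 kg gives 39, then 44. A one-sided test at SD 11.7 gives 37, then 42. The stated power therefore rests on 45 analysable women per arm.

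**2. Power under loss** (8 kg, SD 11.7, two-sided). Only the 10% figure is in the article; higher losses are a sensitivity range.

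| Loss | Analysed per arm | Power |
|---|---|---|
| 0% | 50 | 92.8% |
| 10% (planned) | 45 | 90.0% |
| 15% | 42.5 | 88.3% |
| 20% | 40 | 86.4% |
| 30% | 35 | 81.6% |

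At the planned loss there is no shortfall.

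**3. Completer against all-randomised difference.** Assume completers differ by 8 kg, a fraction d = 0.10 of the intervention arm drops out and keeps a share k of the effect, and control drop-outs resemble control completers. Then:

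all-randomised difference = 8 × (1 − d) + 8 × k × d

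- k = 0: 7.2 + 0 = 7.2 kg; completers overstate by 0.8 kg.
- k = 0.5: 7.2 + 0.4 = 7.6 kg; completers overstate by 0.4 kg.
- k = 1: 7.2 + 0.8 = 8.0 kg; no gap.

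The article gives no value for k.

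**4. Does the timing conflict produce the completer analysis?** Baseline and post-intervention weights are set for both arms, and the stated between-group comparison is post-intervention. Two cases follow:
- Week 12 is not a time level: a baseline/post ANOVA works for both arms, and only drop-out makes it completer-based.
- Week 12 is a level and controls have no week-12 weight: all 50 controls would be removed, so that model could not be run.

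The two points are therefore separate.

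**5. Timing of the other outcomes.** Fitness and biomarkers name no week-12 point. Under the Outcome measures default they are before-and-after only. Under the Randomisation sentence they are also due at week 12. The default rule gives a usable reading, but the two sentences still differ.

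**The case against.** The strongest reply is that this is a condensed article. Nothing in it says that drop-outs are discarded, and analysis sets and missing-data rules commonly sit in a full protocol or analysis plan that is not shown. Enlarging N allows for lost information; it does not prove that available data will be excluded. That stands, and the absence of missing-data rules is not the point here. What remains is that a method is named, and in its classical form that method is complete-case.

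On timing, it can fairly be said that the Randomisation sentence is a design summary, that the Outcome measures section sets a default with exceptions, and that the article nowhere says controls are not weighed at week 12. This softens the fitness and biomarker part to a wording difference. It does not settle the control weight.

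Three stronger readings are tempting but unsupported:
- A reader might infer that the missing control week-12 weight is what makes the comparison completer-only. Step 4 shows it is not.
- A reader might infer that the intervention arm's weekly weights give its drop-outs a late value that biases the result. An analysis that excludes drop-outs does not use those values, and nothing in Data Analysis carries them forward.
- A reader might infer that the trial is underpowered. At the planned 10% it is not.

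It is also fair that a mixed model assumes data missing at random, so it would not by itself recover 7.2 kg if drop-out depends on weights never seen.

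**Conclusion.** Both points hold, separately. Followed as written, the body-weight comparison is completer-based, with a risk of bias towards the intervention because the attendance burden falls on one arm. The size is illustrative only: 0.4 to 0.8 kg on an 8 kg difference at 10% drop-out, if intervention drop-outs keep between half and none of the effect. The gap is nil if they keep all of it and larger if they gain weight. The issue is bias and which population the estimate describes, not power.

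The Randomisation, Outcome measures and body-weight sections conflict on week-12 control weight and must be reconciled. Fitness and biomarker timing needs the same check. Both changes should be made, though neither shows that the trial cannot answer its question.

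**What to change.** 1. Reconcile the Randomisation, Outcome measures and body-weight sections. State that both arms are weighed at baseline, week 12 and after week 24, with the control week-12 weight taken at the visit already due for impedance and girths. State whether fitness and biomarkers are measured at week 12.
2. For body weight, replace the ANOVA with a likelihood-based linear mixed model on all randomised women by allocated group, with baseline weight as covariate and weeks 12 and 24 as outcomes. SPSS can fit it. Keep the intervention arm's extra weekly weights out of the between-arm comparison.
3. Seek a week-24 weight from women who stop the programme. This step, rather than the model, addresses drop-out that depends on unseen weights.

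**Cost.** Slightly more analysis work, one extra weighing per control, and a return request to about 10 women (10% of 100). N stays at 50 per arm. For 8 kg at SD 11.7, power lies between 90.0% (nothing recovered from drop-outs) and 92.8% (everything recovered). If the all-randomised difference were 7.2 kg, power with all 50 per arm would be 86.8% at SD 11.7 and 91.5% at SD 10.8. These figures take no credit for baseline adjustment.

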### Other outcome measures

#### Psychological indices, cardiorespiratory fitness and quality of life

##### Psychological stress

Psychological stress will be assessed using the Perceived Stress Scale (PSS) [95]. The PSS is one of the most widely used psychological instrument for measuring the perception of stress. It measures the degree to which situations in an individual's life are appraised as stressful. The items evaluate how unpredictable, uncontrollable, and overloaded respondents find their lives. The scale also includes a number of direct queries about current levels of experienced stress. Psychological stress will be assessed in the week before and after the intervention period and at the mid-intervention time point of 12 weeks.

##### Depression

Depression will be assessed using the Beck Depression Inventory II (BDI-II) [96]. The BDI is a 21-item test which measures the presence and degree of depression in respondents. It assesses specific symptoms or attitudes which appear to be specific to depressed patients, and which are consistent with descriptions of the depression contained in the psychiatric literature. Depression will be assessed in the week before and after the intervention period and at the mid-intervention time point of 12 weeks.

##### Cardiorespiratory fitness

Cardiorespiratory fitness will be assessed using a single-stage submaximal treadmill walking test [97]. Improved cardiorespiratory fitness in breast cancer patients following a 16 week exercise intervention has previously been demonstrated using this treadmill test [98]. This test is also being used successfully in our laboratory to assess physiological adaptations resulting from exercise therapy in an ongoing breast cancer trial [91].

##### Quality of life

The Functional Assessment of Cancer Therapy-General (FACT-G) and (FACT-B) [99] will be used to assess quality of life. Quality of life is an important clinical outcome and the FACT-G and FACT-B collectively measure five aspects of quality of life: physical, functional, emotional, social and additional concerns specific to breast cancer. Quality of life will be assessed in the week before and after the intervention period and at the mid-intervention time point of 12 weeks.

##### Physical activity behaviour

Physical activity behaviour at the baseline, and at weeks 6,12,18 and 24 will be assessed using the Stanford Seven-Day Physical Activity Recall (PAR) [100], which has been used successfully in a number of studies. This will be administered by telephone in the control patients.

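### The activity recall is set to telephone for control patients only, so its post-intervention comparison between arms is confounded with how it was administered

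*Protocol article*

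**What the plan says.** Under Physical activity behaviour, the protocol article schedules the PAR at baseline and at weeks 6, 12, 18 and 24, and then states: "This will be administered by telephone in the control patients". It gives no mode for intervention patients and does not say who administers the PAR in either arm. The section falls under Other outcome measures.

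The Data Analysis section plans a mixed factorial ANOVA for "changes from baseline on all outcome measures following the intervention within patient groups" and for differences between the two groups after the intervention.

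Three other places bear on the point:
- Supervised exercise brings intervention patients on site three to five days a week, "for a period of 24 weeks under the supervision of an exercise scientist". The activity log and the pedometers are described only in that section: "portable pedometers (Omron Healthcare, UK) will be used to determine the number of steps/distance walked each day".
- Dietary energy restriction adds, for the intervention arm, a weekly contact: "Once a week, patients will meet with the research assistant who will discuss their individual diet diaries with them".
- Randomisation describes "outcome measures being assessed in the week before and the week after the intervention period and at the mid-intervention time point of 12 weeks". It mentions no visit at weeks 6 and 18.

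**The concern.** This is a stated data-collection rule that differs by randomised arm. It is not a detail held over for another document. The sentence about controls has a purpose only if intervention patients are asked in some other way, and their frequent attendance makes in-person administration the likely alternative.

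The PAR is self-reported by patients who know their allocation. If answers depend on the mode of asking, the between-arm difference in reported activity mixes a real difference with a mode effect. For the post-intervention comparison, no model can separate them, because neither arm is described as using both modes.

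At stake is the evidence on the activity contrast: how far the arms differed in exercise, and how much exercise the controls took up. No other measure of activity behaviour is described for both arms.

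**Working it through.** **1. The plan's only sample-size figure, to see whether it is touched.** Inputs from Details of power calculations and sample size: difference 8 kg, SD 11.7 kg, α 0.05 (two-sided assumed), power 90%, drop-out up to 10%.

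n per arm = 2 × (1.960 + 1.282)² × (11.7 / 8)² ≈ 45 after rounding up; 45 / 0.90 = 50.

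The stated 50 per group reproduces, and normal-approximation power with 45 per arm is 0.900. The calculation concerns body weight, which does not depend on how the PAR is administered. The document gives no figure for the PAR itself.

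**2. What is known about mode.**

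| | Control arm | Intervention arm |
|---|---|---|
| PAR mode | Telephone (stated) | Not stated; another mode implied |
| PAR interviewer | Not stated | Not stated |
| Log and pedometer | Not described | Described |
| Treadmill fitness test | Yes | Yes |

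The text does not settle whether the telephone rule for controls also covers the baseline PAR.

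**3. Where a mode effect would enter.** Let δ₀ be the between-arm difference in mode effect at baseline and δ₁ the same difference after the intervention.

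- Bias in the post-intervention comparison = δ₁.
- Bias in the between-arm difference in change from baseline (the group-by-time contrast) = δ₁ − δ₀.

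| Situation | Post-intervention | Change from baseline |
|---|---|---|
| Arm-specific modes from baseline on, constant effect (δ₀ = δ₁) | δ₁ | 0 |
| Common mode at baseline (δ₀ = 0) | δ₁ | δ₁ |
| Arm-specific modes throughout, effect varies over time | δ₁ | δ₁ − δ₀, not zero |

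The post-intervention comparison carries the bias in every row. Change from baseline is protected only in the first.

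**4. Illustration of size.** Assume 45 evaluable per arm, a two-sided 0.05 test, no true difference in activity, and a mode-related shift of b standard deviations. The standard error in SD units is √(2/45) = 0.211, and

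false-positive rate = Φ(b/0.211 − 1.96) + Φ(−b/0.211 − 1.96).

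| b (SD), assumed | False-positive rate |
|---|---|
| 0 | 5.0% |
| 0.1 | 7.6% |
| 0.2 | 15.8% |
| 0.3 | 29.6% |
| 0.5 | 66.0% |

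The values of b are assumptions. The document supports no particular one.

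**The case against.** The strongest reply has four parts.

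*The intervention mode is never stated.* This is true, and the point rests on an inference. It is a fair one, because the sentence would not single out controls if both arms were telephoned.

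*Change from baseline deals with it.* The Data Analysis section does analyse change, and the baseline PAR is listed together with the follow-ups. If controls are also telephoned at baseline and the mode effect is constant, it cancels in the group-by-time contrast. This stands for that case, but it does not rescue the post-intervention comparison, and the document does not establish that the case applies.

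*The measure is ancillary, and other evidence exists.* PAR appears in no primary or secondary aim. The treadmill test gives evidence of a fitness difference that does not depend on how the PAR is asked. Both statements are correct and limit the importance of the point. Fitness is nevertheless not activity behaviour, and the test would not show how much exercise controls took up.

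*There is a practical reason.* With no visit described at weeks 6 and 18, the telephone suits controls. That explains calling controls but not restricting calls to them.

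A reader might also infer that the interviewer differs by arm, with intervention patients reporting to their own trainer and therefore over-reporting. The document does not support this. Neither the exercise scientist nor the research assistant is named as administering the PAR, one person could interview both arms, and nothing gives the direction of a mode effect.

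**Conclusion.** The concern holds in a limited form. As written, the mode of the PAR is tied to arm, and the post-intervention comparison of physical activity is confounded with it. The between-arm difference in change from baseline is also affected if the baseline mode is common to both arms or if the mode effect varies over time.

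This rests on one inference, that intervention patients are not telephoned. The size and direction of any bias are unknown, so the false-positive rates above show sensitivity and are not estimates. It would go too far to say that any mode effect passes in full into every PAR analysis, since a constant effect can cancel in change scores.

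Body weight, its sample size and its power are unaffected. The change is worth making because PAR is the only activity-behaviour measure described for both arms, and because analysis cannot separate mode from arm in the post-intervention comparison once the data are collected.

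**What to change.** Replace the sentence on control patients under Physical activity behaviour with wording such as: *PAR will be administered by telephone in both groups at baseline and weeks 6, 12, 18 and 24, using the same script.* Preferably, the calls are made by existing staff who do not supervise that patient's exercise sessions. Because staffing is not described, this is a preference and the main change does not depend on it.

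The cost is one sentence and the same number of interviews. Calls would replace any convenient on-site interviews in the intervention arm. A common mode removes the mode confound only: intervention patients know that they are in an exercise programme, so some over-reporting may remain.
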